#### Data management

An individual code will be used to identify each participant in this study. Only one of the two principal investigators ([name]) will have access to the database and shall be responsible for its management.

#### Statistical methods

Numerical variables will be expressed descriptively as mean and standard deviation (SD). Student *t*-test for paired data will be used to compare the quantitative variables before and after the intervention, and Student *t*-test for independent samples for inter-group comparison of pre- and post-intervention changes. At a later stage, mixed models will be performed to test changes in parameters and the between-group differences in evolution, adjusting by possible confounders. The evaluation of the correlations between variables will be based on the quantitative variables obtained from the various studies and bivariate (ordered Spearman correlation) and multivariate (multiple regression) analysis. Reasons for protocol non-adherence will be registered. The level of alpha risk accepted for all tests will be 0.05.

The evaluation of the correlations between variables will be based on the quantitative variables obtained from the various studies and bivariate (ordered Spearman correlation) and multivariate (multiple regression) analysis. Reasons for protocol non-adherence will be registered and missing data will be discarded. The level of alpha risk accepted for all tests will be 0.05.

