### Outcome measures

Main outcome variable:
Change in dysphagia severity observed by VFSS and assessed with the Penetration-Aspiration Scale: scores 1–2 indicate normal swallowing, 3–5 penetration, and ≥ 6 aspiration

Secondary outcome variables:
Change in quality of life, assessed with the European Organization of Research and Treatment of Cancer (EORTC) Quality-of-Life Questionnaire (QLQ-C30) and its Head and Neck Cancer Module (QLQ-H&N35).Mouth opening or the maximal interincisor opening (MIO) of the mouth, using the Therabite® range of motion scale.Maximum isometric tongue pressure in an anterior position.Maximum inspiratory and expiratory pressures (PImax and PEmax, respectively).Impaired security (tone of voice, coughing during or after eating, or desaturation > 3% compared to baseline pulse oximetry) and efficacy in oral and pharyngeal phases of swallowing with the use of the Volume-Viscosity Swallow Test.Subjective difficulty of swallowing assessed by a Visual Analogic Scale (VAS) ranging from 0 to 10; a low score indicates no difficulties in eating and a high score, no oral intake.Peak cough flow (PCF) will be used to evaluate the effect of IEMT on voluntary cough. It is measured with spirometer in liters/minute. Patients will be instructed to perform three repetitions of voluntary cough and the best one will be chosen.

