### Sample size calculation

Accepting an alpha risk of 0.05 and a beta risk of 0.2 in a two-sided test, a total sample size of 52 patients will be required to detect a difference ≥ 10 (SD 11) units in the test of quality of life and 2 (SD 2.3) units in the PAS. In order to account for estimated 20% loss to follow-up, five patients have been added, resulting 26 patients on each group.

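### The PAS is compared by an unadjusted t-test on change, which gives up power and cannot be read as a shift between the protocol's own severity bands

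*Protocol article*

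**What the plan says.** Outcome measures, in the protocol article, defines the main outcome as "Change in dysphagia severity observed by VFSS and assessed with the Penetration-Aspiration Scale", and adds that "scores 1–2 indicate normal swallowing, 3–5 penetration, and ≥ 6 aspiration".

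Sample size calculation sets its target in scale units, "2 (SD 2.3) units in the PAS", under the terms "Accepting an alpha risk of 0.05 and a beta risk of 0.2 in a two-sided test".

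Statistical methods says that a paired t-test "will be used to compare the quantitative variables before and after the intervention", and gives a t-test "for independent samples for inter-group comparison of pre- and post-intervention changes". It then says "At a later stage, mixed models will be performed to test changes in parameters and the between-group differences in evolution", adjusted for possible confounders. The type of mixed model and the confounders are not given. PAS is not named among the quantitative variables; that it is meant rests on its being sized in units with an SD. The bands from Outcome measures do not reappear.

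**The concern.** Two things follow from comparing mean change on this scale.

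- **Interpretation.** The bands are what give a PAS score its meaning, and equal unit steps are not equal steps between bands. A difference of 2 units could mean that early exercise kept many patients out of mild penetration, or that it kept a few out of deep aspiration. The aim is to preserve swallow function, so a reader will want to know which.
- **Efficiency.** A raw change score subtracts the whole starting score, whatever its correlation with the follow-up score. Unless that correlation is close to 1, regression on the starting score gives a more precise comparison. With 26 patients per arm before losses, the difference matters.

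**Working it through.** **1. The plan's own figure.** Inputs from Sample size calculation: difference 2, SD 2.3, two-sided alpha 0.05, power 0.80.

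n per arm = 2 × (1.960 + 0.842)² × 2.3² / 2² = 20.8, so 21 per arm and 42 in total. Adding five per arm gives 26 per arm and 52 in total, the stated size. The quality-of-life inputs (10, SD 11) need only 19 per arm, so PAS drives the size. Sizing and t-test agree with each other.

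**2. Units against bands.** I assume a top score of 8, which the article does not state. The six possible 2-unit worsenings are 1→3, 2→4, 3→5, 4→6, 5→7 and 6→8. Two of them (3→5, 6→8) change no band. The 1-unit step 5→6 enters aspiration, while 1→2 stays normal.

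With 21 patients per arm, a mean difference of 2 is 42 units in total. It can arise from 21 patients each moving 2→4 (21 × 2 = 42: all to penetration, none to aspiration) or from 7 patients each moving 2→8 (7 × 6 = 42: a third to aspiration). The planned estimate is the same in both cases.

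**3. Cost of not adjusting.** Let σ be the SD of a score at one visit (taken as equal at t0 and follow-up) and ρ the correlation between the two.

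- Variance of change: 2σ²(1 − ρ)
- Variance after adjustment for t0: σ²(1 − ρ²)
- Ratio, adjusted to change: (1 + ρ)/2

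Power ≈ Φ(2/s × √(21/2) − 1.960), with s the relevant SD. The article does not say whether 2.3 is the SD of change or of a score, so both are shown. ρ is assumed.

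| ρ | 2.3 read as | SD of change | SD adjusted | Power, change | Power, adjusted | Gain (points) |
|---|---|---|---|---|---|---|
| 0.3 | SD of change | 2.30 | 1.85 | 80% | 94% | 13 |
| 0.5 | SD of change | 2.30 | 1.99 | 80% | 90% | 10 |
| 0.7 | SD of change | 2.30 | 2.12 | 80% | 86% | 6 |
| 0.3 | SD of score | 2.72 | 2.19 | 66% | 84% | 18 |
| 0.5 | SD of score | 2.30 | 1.99 | 80% | 90% | 10 |
| 0.7 | SD of score | 1.78 | 1.64 | 95% | 98% | 2 |

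**4. Skewed eight-level scores.** Simulation with 21 per arm, latent correlation 0.5, latent shift 0.9 between arms and 2,000 runs. The distributions are assumed.

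| Share scoring 1–2 (baseline / late-arm follow-up) | t-test on change | ANCOVA on PAS units |
|---|---|---|
| 75% / 60% | 52% | 69% |
| 60% / 28% | 67% | 84% |
| 60% / 60% | 45% | 71% |
| 28% / 28% | 70% | 85% |

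With a shift of 0.5 the gains were 6 to 10 points. Two further sets of assumed distributions gave 1 to 16 and 4 to 18 points. With no treatment effect the change t-test rejected in 4.4% to 5.4% of runs. A rank test on the same change gained only −1 to +2 points, so the loss comes mainly from the unadjusted change and not from treating PAS as a number.

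**5. Would an ordinal primary analysis do better?**

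- *Proportional shifts* (600 runs): a proportional-odds model with arm and t0 PAS had 86%, 78% and 86% power against 84%, 71% and 83% for ANCOVA. A second set of runs gave 0 to 4 points over ANCOVA; a repeat of the four cases above (400 runs each) gave 1 to 9.
- *A minority moving deep into aspiration.* Assumed band proportions (normal/penetration/aspiration) are 55/39/6% in the early arm and 38/16/46% in the late arm, with means 2.55 and 4.54. On follow-up scores alone, the t-test had 76% power and the rank test 46%. With baseline included, in cases of this kind, the t-test or ANCOVA had 59–86%, the proportional-odds model 47–62% and the rank test 39–49%.

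**The case against.** The strongest reply is that outcome, sizing and test are consistent. The protocol says severity is assessed with the PAS, sizes in PAS units and compares changes; the bands can be read as a key to the scores. The t-test is valid, the later mixed models may adjust for baseline, and a condensed article may leave model details to an analysis plan that is not shown. Most of this stands. It does not remove the point, because the article states a between-group test, and that test is inefficient and does not use the bands.

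A reader might go further in four ways that the documents do not support.

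- *The t-test does not measure severity as defined.* It does: severity is scored with the PAS, and the target is 2 PAS units.
- *The t-test is in general the less powerful test.* That holds under proportional shifts and fails when a minority of patients worsen greatly.
- *An ordinal analysis can only gain.* The second case in step 5 shows losses.
- *An SD of 2.3 is impossible near the floor.* On a 1–8 scale the SD at mean m is at most √((m − 1)(8 − m)), which is 1.80 at m = 1.5. That bounds the scores of one arm at one visit. The planned variable is change, and 2.3 may be pooled: arm SDs of 1.53 and 2.95 pool to √((1.53² + 2.95²)/2) = 2.35.

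A heavy floor is itself an inference. Entry does not require dysphagia, and Background says many patients regain swallowing by 3 months. But patients have advanced disease, Background also describes later deterioration, and no PAS distribution is given.

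**Conclusion.** The point holds in a limited form. The planned comparison is valid and matches the sizing, but its estimate cannot be translated into movement between normal, penetration and aspiration, and leaving out the t0 score as a covariate gives up power. The band mismatch follows from the protocol's own cut-offs; only the 6→8 example needs the assumed top score of 8.

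The power loss is conditional. It is about 2 to 18 points on the planning figures with ρ from 0.7 to 0.3, and tends to nothing as ρ nears 1. Skewed simulations gave 1 to 26 points, the top value coming from one floor-heavy case. All of this rests on correlations and distributions that the documents do not give.

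The evidence favours baseline adjustment. It does not show that an ordinal primary analysis is needed: that gains 0 to 9 points over ANCOVA under proportional shifts and can lose more than that when a few patients aspirate badly.

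**What to change.** In Statistical methods, for the PAS:

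- Make the between-group comparison an analysis of follow-up PAS by arm with t0 PAS as a covariate (ANCOVA). This keeps the effect in PAS units and comparable with the 2-unit target. t0 comes before any exercise in either arm.
- Report by arm the proportions with normal swallowing, penetration and aspiration, using the cut-offs in Outcome measures. Keep this descriptive: in the simulations, a yes/no test for aspiration had 14 to 35 points less power than the planned t-test.
- Prespecify a proportional-odds model with arm and t0 PAS as a supporting analysis, with its assumption checked. Making it primary is optional, given the trade-off above.

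The cost is one covariate and slightly more reporting. No new patients or data are needed, since a change score already requires the t0 value. The change should be settled before the arms are compared.

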**Methods/design:**

The Redyor study is a single-blind randomized clinical trial designed to compare the effect of prophylactic oropharyngeal exercises on quality of life and dysphagia of 52 patients with HNC referred to the Radiotherapy Department. The intervention will consist of respiratory muscle training (3 times/day, 5 days/week, 21 weeks) added to the standard swallow therapy. All patients will perform the same exercise intervention, but at different times: before chemoradiotherapy (CRT; early intervention group) or immediately after completing CRT (late intervention group). The main outcome will be change in dysphagia severity assessed with the Penetration-Aspiration Scale in videofluoroscopy study; quality of life will be assessed with the EORTC-QLQ-C30 and its Head and Neck Cancer Module (QLQ-H&N35) at 3, 6, and 12 months after completing CRT.

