## Background

Squamous head and neck cancer (HNC) has high incidence in developed countries. HNC is categorized according to the area of the head or neck in which it occurs, with greater incidence in the larynx, followed by the oropharynx, oral cavity, and hypopharynx. At the time of diagnosis, 1% of all patients have a distant metastasis, with the highest rate (4%) observed in the nasopharynx and earlier-stage tumors located in the larynx and the oral cavity. Tobacco and alcohol use and human papilloma virus (HPV) infection are the most important risk factors [1].

Although chemo-radiation therapy (CRT) protocols have been designed to preserve swallowing function and essential speech organs, dysphagia is a frequent symptom in these patients and the primary adverse effects are usually associated with acute or late swallowing disturbances [2–6]. Preservation of underlying anatomical structures does not guarantee normal function. CRT affects target areas and may result in lack of coordination of swallowing phases, lack of swallow coordination with respiratory function, reduced elevation of larynx, delayed laryngeal closure, loss of tongue strength, and prolonged oral and pharyngeal time in swallowing [6–9]. Radiation-induced dysphagia pathogenesis includes an initial process of acute inflammation with the appearance of edema, which may be followed by fibrosis of the soft tissues resulting in neurological alteration and muscle damage. Xerostomia, pain, and pharynx obliteration are the key elements of acute-phase dysphagia. At 3 months, many patients have regained swallowing function. In later stages, with the appearance of diffuse fibrosis of the connective tissue and skin in the irradiated area, changes are observed in the efficacy and safety of swallowing. It is believed that hypoxia and chronic oxidative stress could perpetuate tissue damage even long after the end of treatment, which would explain the appearance of dysphagia in the chronic phase [10]. These side effects contribute to higher rates of malnourishment, weight loss, and bronchoaspiration [6, 11], resulting in a need for alternative or supplementary methods for feeding and hydration, both early and long-term [8].

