### Intervention

The training protocol consists of IEMT and standard swallowing exercises. Patients will be instructed to maintain a rate of 15–20 breaths/min using the Orygen-Dual® valve (described elsewhere in detail) [21, 22], a respiratory device that allows patients to train inspiratory and expiratory muscles simultaneously. Training loads will be set at a pressure equivalent to 10 maximal repetitions (if tolerated). These external pressures will be regulated weekly at 30% of maximal inspiration/expiration respiratory measures obtained. Patients will be instructed to perform 3 sets of 5 repetitions and standard swallowing exercises (mobility and tonicity exercises of the tongue, palate, larynx, and constrictor muscles), 3 times/day, 5 days/week, for 21 weeks. An experienced swallowing therapist will supervise IEMT weekly. The protocol will be the same for both groups, but one group will start 2 weeks before CRT and the other one will begin immediately after completing CRT (Fig. 1).

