### Participant timeline

Eligible patients will be randomized and referred to the Rehabilitation Department for function assessment and intervention. The study outcomes will be assessed at baseline (2-week pre-CRT, t_0_), at the beginning of CRT (t_1_), at the end of CRT (t_3_), and thereafter at 3 months (t_4_), 6 months (t_5_), and 12 months (t_6_). The Redyor schedule of enrollment is shown in Fig. 2.

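### Read literally, the between-group t-test on change before and after the exercise programme compares a window that contains all of CRT with one that contains none of it

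*Protocol article*

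**What the plan says.** All of this is in the protocol article.

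- **Statistical methods** anchors both t-tests on the intervention. The paired test "will be used to compare the quantitative variables before and after the intervention", and the two-group test is for "independent samples for inter-group comparison of pre- and post-intervention changes". Mixed models for between-group differences in evolution follow at a later stage. Neither analysis is called primary.
- **Abstract, Methods/design** shows that the intervention is the exercise programme, not CRT: "All patients will perform the same exercise intervention, but at different times".
- **Intervention** sets the timing: "one group will start 2 weeks before CRT and the other one will begin immediately after completing CRT". The prescribed course is the same in both arms: "3 times/day, 5 days/week, for 21 weeks".
- **Outcome measures** gives the main outcome as "Change in dysphagia severity observed by VFSS and assessed with the Penetration-Aspiration Scale", with no start or end visit for the change.
- **Participant timeline** gives one schedule for both arms: t0 (2 weeks before CRT, called baseline), t1 (start of CRT), t3 (end of CRT), then t4, t5 and t6 at 3, 6 and 12 months.
- **Background** says that CRT impairs swallowing, and describes the later course: "At 3 months, many patients have regained swallowing function".

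**The concern.** Randomisation makes the two arms comparable at t0 and at any later time counted from the same origin. It does not make one arm's t0 comparable with the other arm's t3. If the value before the intervention is taken as each arm's own programme start, the early change contains the injury from CRT and part of the recovery. The late change starts once that injury has happened and contains mostly recovery.

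The between-group difference would then mix the effect of timing, which the trial is meant to estimate, with the effect of CRT itself, which both arms receive. Because CRT is expected to worsen swallowing, the distortion generally makes the early arm look worse. That is the arm the trial expects to do better, so a real benefit could be masked. The rule covers the quantitative variables in general, so quality of life is exposed as well as PAS.

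**Working it through.** **The plan's own figure.** Sample size calculation gives two-sided alpha 0.05, beta 0.2, and a PAS difference of 2 with SD 2.3.

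n per arm = 2 × (1.960 + 0.842)² × 2.3² / 2² = 2 × 7.849 × 5.29 / 4 = 20.8, rounded up to 21. Adding 5 gives 26 per arm, 52 in total, as stated. With the t distribution, power at 21 per arm is 78.5%. I use 21 per arm (after the planned losses) and 26 (no losses).

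**The two windows.** CRT length L is not stated; I assume 5 to 8 weeks. Times are in weeks from the start of CRT.

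| Arm | Programme start | Programme end | End, relative to end of CRT | CRT inside window |
|---|---|---|---|---|
| Early | −2 (t0) | −2 + 21 = 19 | 19 − L = 14 to 11 weeks after | all |
| Late | L (t3) | L + 21 | 21 weeks (about 4.8 months) after | none |

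The late arm's programme end falls between t4 (3 months) and t5 (6 months), where no visit is scheduled.

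**Difference between arms when timing has no effect.** Let both arms follow the same mean PAS course Y. Let a = Y(t3) − Y(t0) be the worsening over CRT. Let r_E and r_L be the fractions of a recovered by the early and late window ends.

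- Early change = a(1 − r_E)
- Late change = −a·r_L
- Bias B = a(1 − r_E) + a·r_L = a(1 + r_L − r_E)

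If r_E = r_L, then B = a, whatever the amount of recovery. If r_E = 0.50 and r_L = 0.75, then B = 1.25a. A positive B makes the early arm look worse, because higher PAS is worse.

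**Rejection rate under that null.** The standard error is 2.3 × √(2/21) = 0.710 at 21 per arm. The noncentrality is B/0.710, on 40 degrees of freedom. The document does not give a, so the values below are assumptions.

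| Assumed B (PAS units) | 21 per arm | 26 per arm |
|---|---|---|
| 0.5 | 10.6% | 12.0% |
| 1.0 | 28.0% | 33.7% |
| 1.25 (a = 1, unequal recovery) | 40.5% | 48.5% |
| 2.0 | 78.5% | 86.7% |

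A simulation of 20,000 trials with B = 1 and 21 per arm rejected 27.7% of the time. With one common window for both arms under the same null, it rejected 4.9%.

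**Effect on power.** If early training truly lowers PAS by the planned 2 units and B = 1, the expected observed difference is 2 − 1 = 1 unit. Power at 21 per arm falls from 78.5% to 28.0%.

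**The case against.** The strongest reply is that the authors probably meant a common window. Participant timeline calls t0 the baseline for everyone and counts visits from CRT in both arms. The hypothesis in the Abstract expects a smaller loss of quality of life with early training, which makes sense only if both arms are measured from before CRT. The literal window cannot even be run on the schedule, because the late arm has no visit at its programme end. Mixed models of between-group evolution are also planned and could give the valid contrast. The flow and SPIRIT diagrams are not available here.

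Most of this stands as evidence of intent. None of it ties the t-test to t0 or names the visit at which change ends. Statistical methods anchors the test on the intervention in both of its clauses, and an analyst who follows that wording takes different starting points in the two arms. This is a stated rule that does not suit the design, rather than a detail left to another document.

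The objection also limits the size of the claim. No PAS worsening is given. Only dysphagia from causes other than cancer is excluded, so swallowing may already be impaired at t0 and the net change over CRT is uncertain. Equality of bias and worsening needs equal recovery at two window ends that are weeks apart.

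A reader might infer that the trial's primary test is invalid, or that the plan throws away what randomisation gave. The document supports neither. It names no primary test, and the common visits keep the randomised comparison available.

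**Conclusion.** The point holds as a defect in the wording of the analysis rule. As written, the between-group t-test sets a change that includes all of CRT against one that includes none. On the Background's own account of what CRT does to swallowing, the arms would then differ with no effect of timing, generally against the early arm. A valid comparison is within reach from the scheduled visits, but the text does not commit to it.

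The size is illustrative only. Rejection of a true null at about 11%, 28% or 79% rests on an assumed CRT worsening of 0.5, 1 or 2 PAS units, equal recovery at both window ends, SD 2.3 applying to the change score, and 21 per arm. It would be wrong to infer from these figures that the trial's result will be reversed, or that the authors certainly intend arm-specific windows. The wording should still be corrected before any between-group result is produced, because nothing in it prevents the biased version from being the one reported.

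**What to change.** In Statistical methods, state that for every between-group comparison, change is measured in both randomised arms from t0 to the same named visit timed from the end of CRT. Alternatively, make the mixed model over the common visits, with t0 as baseline, the main between-group analysis. The paired test can keep its programme-based wording if it is described as within-arm and descriptive.

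The common t0 anchor and the common visit are what remove the bias. The choice of visit is secondary. The 6-month visit (t5) is reasonable because it is the first scheduled visit after both arms have completed 21 weeks; at 3 months (13 weeks) the late arm has done 13/21 = 62% of the programme. Another named visit would also remove the bias, but would answer a somewhat different question.

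The cost is one sentence. The visits are already scheduled in both arms, and the total of 52 is unaffected if SD 2.3 applies to the newly defined change. Because Trial status puts the end of data collection at 04/29/2019, the clarification should be dated and should say whether outcome data by arm had been seen when the visit was chosen.

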### Data collection, management, and analysis

#### Data collection methods

The main outcomes will be collected by means of a Data Collection Logbook specially designed for this study. This logbook will include the EAT-10 and both quality of life questionnaires (EORTC-QLQ-C30 and QLQ-H&N35). One member of the investigation team ([name]) shall be responsible for the collection and processing of data related to main outcome variables. To promote participant retention, patients will perform a weekly supervised session; any patient not attending these scheduled sessions will be contacted by telephone.

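### No visit or model is named as deciding for the Penetration-Aspiration Scale, so the 5% error rate behind the sample size is not secured

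*Protocol article*

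**What the plan says.** All references are to the Protocol article.

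- **Outcome measures** gives the main outcome as "Change in dysphagia severity observed by VFSS and assessed with the Penetration-Aspiration Scale". It names no visit.
- **Participant timeline** starts "The study outcomes will be assessed at baseline (2-week pre-CRT" and goes on to t1 (start of CRT), t3 (end of CRT), t4 (3 months), t5 (6 months) and t6 (12 months). That makes five post-baseline visits; no t2 is listed.
- The **abstract** gives "at 3, 6, and 12 months after completing CRT", in the clause on quality of life.
- **Intervention** has both arms follow the same 21-week programme. One starts two weeks before CRT, the other immediately after CRT.
- **Statistical methods** plans an independent-samples t-test on pre- to post-intervention change and, later, mixed models of the between-group difference in evolution. It then says "The level of alpha risk accepted for all tests will be 0.05".
- **Sample size calculation** opens "Accepting an alpha risk of 0.05 and a beta risk of 0.2 in a two-sided test". It sizes the trial on a PAS difference and a quality-of-life difference, again without a visit.

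**The concern.** A confirmatory result needs one comparison fixed in advance: which visit, against which baseline, by which model. The article fixes none of these for PAS. It also sets the same 0.05 level for every test, so this is a stated rule and not mere silence on multiplicity.

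The staggered start makes the gap more than a formality. Read literally, the pre-intervention value is t0 in the early arm but about t3 in the late arm, where it is measured after randomisation and after CRT. The post-intervention value also falls at different times after CRT in the two arms. The choice of visit therefore changes the question as well as the p-value. If it is made after results are seen, a positive claim could rest on whichever visit is favourable, and the 5% error rate assumed in the sample size would not apply to it.

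**Working it through.** **1. The plan's own figure.** Inputs from Sample size calculation: difference 2, SD 2.3 (PAS); difference 10, SD 11 (quality of life); two-sided alpha 0.05; power 0.80; 20% loss.

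n per arm = 2 × (1.960 + 0.842)² × (SD/difference)²

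- PAS: 2 × 7.85 × 1.3225 = 20.8, so 21 per arm.
- Quality of life: 2 × 7.85 × 1.21 = 19.0, so 19 per arm.
- Loss: 21 × 1.2 = 25.2, so 26 per arm and 52 in total. Dividing instead, 42/0.8 = 52.5, so 53.

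The stated 52 reproduces, for a single PAS test at 0.05.

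**2. What each visit compares.** The late arm starts at the end of CRT. The early arm finishes 21 − 2 = 19 weeks after the start of CRT.

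| Visit | Early arm | Late arm |
|---|---|---|
| t1, start of CRT | 2 of 21 weeks | not started |
| t3, end of CRT | trained for 2 weeks plus the length of CRT, up to 21 weeks | not started |
| t4, 3 months | finished if CRT lasts 6 weeks or more (19 − 13) | about 13 of 21 weeks |
| t5, 6 months (about 26 weeks) | finished | finished (26 > 21) |
| t6, 12 months | finished | finished |

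The first visit at which both arms have certainly finished is t5.

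**3. Error rate if every visit is tested and any one counts.** With k independent tests the rate is 1 − 0.95^k. For k = 5 this is 22.6%; for k = 3 it is 14.3%. For tests with equal correlation ρ:

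rate = 1 − ∫ φ(u) [Φ((1.96 − √ρ·u)/√(1−ρ)) − Φ((−1.96 − √ρ·u)/√(1−ρ))]^k du

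| ρ (assumed) | five visits | three visits (3, 6, 12 months) |
|---|---|---|
| 0 | 22.6% | 14.3% |
| 0.5 | 18.3% | 12.5% |
| 0.6 | 16.7% | 11.8% |
| 0.7 | 14.8% | 10.9% |
| 0.8 | 12.7% | 9.8% |
| 0.9 | 10.2% | 8.4% |

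As a check, t-tests on change from baseline were simulated with 21 and 26 patients per arm (40,000 trials per setting). Over five visits they gave 18.1-18.7% with equal correlation among the raw scores and 14.8-16.9% with first-order autoregressive correlation of 0.5-0.9. If one prespecified comparison decides, the rate is 5%.

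**4. Can the last recruit reach t5?** Trial status gives the end of recruitment as 21 August 2018 and the end of data collection as 29 April 2019, which is 251 days. Subtracting 14 days before CRT and about 182 days after it leaves 251 − 14 − 182 = 55 days, or 7.9 weeks, for CRT and any delay. The article does not state how long CRT lasts. The same section also mentions May 2019, which would add up to about a month. On either date the last recruit cannot reach t6, 12 months after CRT.

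**The case against.** The strongest reply is that five separate PAS tests are not what Statistical methods describes. It speaks of one inter-group comparison of change, and then of mixed models that could be summarised in a single group-by-time test. On that reading the rate is 5%. Moreover, t1 and t3 can hardly be post-intervention visits for an arm that has not yet started. The abstract mentions only 3, 6 and 12 months, and the schedule figure, which may restrict when videofluoroscopy is done, is not available here.

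Much of this stands. A reader might infer that the false-positive rate on the main outcome is 15-18%. The documents do not support that as a fact. It requires a test at all five visits, success declared on any one of them, and correlations of 0.5-0.7 between tests, none of which the article states.

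A reader might also infer that the status of the outcomes shifts. Quality of life enters the sample size, and Data collection methods says of the logbook for main outcomes that "This logbook will include the EAT-10 and both quality of life questionnaires". That reading does not hold either. The abstract, the objectives in Background and Outcome measures all put dysphagia first and quality of life second. Sizing on two outcomes does not make both primary, so pooling them into one larger error rate is not justified.

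Handling of multiplicity among secondary outcomes may properly sit in an analysis plan that is not shown.

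What the reply does not supply is the deciding comparison. With staggered training, the single pre/post reading identifies no common visit, and the mixed-model reading leaves its contrast open.

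**Conclusion.** The concern holds in this form: no visit or model is fixed as deciding for PAS, so the 5% error rate assumed in the sample size is not secured. That is weaker than saying it is violated. The rate is 5% if one prespecified comparison decides. If each visit is tested and any one counts, it is about 10-23% over five visits and 8-14% over the three later ones, for assumed correlations from 0.9 down to 0. The 15-18% band applies only to five visits with correlations of 0.5-0.7. All these figures treat the test statistics as normal and equally correlated. The more durable problem is that the visits compare different amounts of training, so leaving the choice open also leaves the meaning of the main result open.

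**What to change.** Before any unblinded analysis, name one confirmatory contrast: the between-arm difference in PAS at one stated visit, adjusted for the t0 value, at two-sided 0.05. The 6-month visit (t5) is a sensible choice, by analysis of covariance or as a contrast from the mixed model already planned. Both arms have finished 21 weeks by then, and the last recruit can reach it if CRT plus any delay takes no more than about 8 weeks. Another visit, or one stated mixed-model contrast, would restore 5% equally well if declared in time.

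Report PAS at the other visits and the secondary outcomes with confidence intervals, as supportive. Trial status dates the end of data collection before the article's publication in August 2019. If the data have already been analysed, report all visits and label the chosen one post hoc, because naming it afterwards does not restore 5%.

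Separately, reconcile the loose main-outcomes wording in Data collection methods with Outcome measures, which does not list the EAT-10 at all.

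Cost: the sample size stays at 52. The change needs a dated amendment, which the article sends to ethics review, and other visits can no longer support a confirmatory claim.
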